## Introduction

The cornerstone of modern pain management in cardiac surgery lies in proactively preventing the development of chronic postsurgical pain (CPSP). This paradigm shift emphasizes pre-emptive interventions to disrupt the cascade of events and central sensitization that transform acute postoperative pain into a persistent, debilitating condition. CPSP, a significant and often underestimated consequence of cardiac surgery, affects a substantial proportion of patients, with prevalence rates ranging from 28% to 56% in the years following surgery. Its impact extends beyond mere discomfort, significantly impairing daily function, reducing quality of life, and imposing a substantial economic burden on the healthcare system.

The pathophysiology of CPSP involves a complex interplay of factors, with central sensitization playing a pivotal role. This process, characterized by heightened neuronal excitability within the central nervous system, amplifies pain signals and can lead to persistent pain even after the initial injury has healed. Therefore, a crucial aspect of CPSP prevention lies in disrupting the afferent nociceptive signals transmitted from the injured tissues to the spinal cord and brain, thereby preventing the establishment and perpetuation of central sensitization.

While opioids have traditionally been the mainstay of postoperative pain management, their use is not without significant drawbacks. Opioids can have dose-dependent side effects, including respiratory depression, nausea, and constipation. Furthermore, prolonged opioid use can lead to tolerance, opioid-induced hyperalgesia, and an increased risk of chronic opioid use. Recognizing these limitations, the current emphasis in pain management is on multimodal analgesia strategies that incorporate non-opioid medications and regional anaesthesia techniques to optimize pain control while minimizing the risks associated with opioid use.

Non-steroidal anti-inflammatory drugs (NSAIDs) offer a valuable adjunct in pain management, but their use in cardiac surgery is often limited due to concerns regarding bleeding complications and potential renal impairment. Other non-opioid analgesics, such as paracetamol and gabapentinoids, have shown limited efficacy in managing the intense pain associated with sternotomy. Regional anaesthesia techniques have emerged as promising

strategies for both acute pain management and potential CPSP prevention in various surgical settings. Techniques such as epidural anaesthesia and paravertebral blocks have demonstrated efficacy in reducing postoperative pain intensity and opioid requirements. However, their application in cardiac surgery presents unique challenges. Epidural anaesthesia carries the risk of neuraxial hematoma due to systemic anticoagulation and heparinization, while paravertebral blocks may be associated with complications such as pneumothorax and pleural puncture. Erector spinae plane block (ESPB) has shown inconsistent results in reducing postoperative pain and morphine consumption in cardiac surgery. Parasternal plane blocks offer advantages over neuraxial techniques but may not adequately address visceral pain.

While regional anaesthesia is crucial for managing acute postoperative pain, its impact on CPSP remains largely unknown. The potential for regional anaesthesia to reduce CPSP has been identified as one of the top research priorities in anaesthesia and perioperative care. Intertransverse process block (ITPB) is a novel and promising alternative, targeting the paravertebral space through extra-paravertebral injection within the intertransverse tissue complex, posterior to the superior costotransverse ligament (SCTL). Recent MRI studies have demonstrated consistent spread of local anaesthetic to the ipsilateral intercostal, paravertebral spaces, neural foramina, and epidural space following ITPB, suggesting potential for both somatic and visceral analgesia. It demonstrated preferential spread of LA to the epidural space and neural foramina over the ESPB, and into the thoracic paravertebral space with effective analgesia after breast and video-assisted thoracoscopic surgeries. Compared to other regional techniques in cardiac surgery, ITPB may offer a simpler and safer approach with reduced risk of pleural puncture and bleeding. Therefore, this trial will assess the analgesic efficacy of ITPB aimed at mitigating both acute and chronic postsurgical pain in cardiac surgical patients. We hypothesis ITPB will reduce CPSP after cardiac surgery, improve pain control, improve quality of recovery and health-related quality of life. The primary aim is to investigate the efficacy of intertransverse process block (ITPB) on CPSP after cardiac surgery by determining the incidence of CPSP at 3-month, defined as persistent pain that was not present before surgery or that had different characteristics, and other possible causes of pain are excluded. The secondary aims are to investigate the quality of recovery after cardiac surgery, and its analgesic efficacy in the immediate postoperative period, and to investigate the efficacy of ITPB on the incidence of CPSP at 6-month and 12-month, and the pain interference (sensory and affective components, physical activities) at 3-month, 6-month and 12-month after surgery.

## Methods

This is a prospective, parallel, double-blinded, randomized controlled trial. Patients undergoing elective cardiac surgery in Prince of Wales Hospital, a university teaching hospital with 1650 beds in Hong Kong, are eligible for enrolment. All patients will be admitted to a 23-bed ICU for early postoperative care and monitored with 1:1 nursing at all times, with an expectation of discharge from ICU to a high-dependency cardiac ward within 24 hours after surgery. Currently, 350-400 adults undergo elective coronary artery bypass graft (CABG) and/or valvular surgery each year.

**Inclusion:** Adult patients aged 18 or older, undergoing elective CABG, valve repair/replacement, or combined CABG/valve procedure via sternotomy, will be included.

**Exclusion:** Emergency surgery, redo surgery, history of chronic pain or being on chronic opioids/sedatives, renal failure with an estimated glomerular filtration rate  $\leq 30$  ml/min (calculated by Cockcroft-Gault formula), re-operation within 24 hours after surgery, intraoperative use of remifentanyl, and inability to provide informed consent.

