### ***Anaesthesia and Interventions***

All patients receive standard cardiac surgery monitoring. General anaesthesia is induced with midazolam 0.01-0.05 mg/kg, fentanyl 2-5 mcg/kg, and rocuronium 0.5-1 mg/kg to facilitate intubation. Anaesthesia is maintained with sevoflurane and propofol infusion, targeting a Bispectral Index of 40-60. ITPB is performed after anaesthesia induction with the patient in lateral decubitus positioning. Intraoperative opioids (fentanyl and morphine) will be administered at the discretion of the anaesthesiologist. The postoperative analgesia protocol was identical in both study groups, including patient-controlled analgesia (PCA) morphine protocol for 72 hours after surgery, oral analgesics (paracetamol 1g every 6 hours, dihydrocodeine 30mg three times a day), and on-demand antiemetics (intravenous ondansetron 4mg every 8 hours). Rescue analgesics on top of the protocol regimen can be prescribed as needed. Upon ICU admission, propofol infusion is stopped to facilitate weaning from ventilator using Adaptive Support Ventilation (ASV), which adjusts the ventilation parameters depending on the patient's lung mechanics and effort. Pain will be assessed regularly in ICU and on the ward. Upon extubation, pain scores are assessed at 2-hour, 4-hour, 8-hour, 12-hour, 24-hour, 48-hour and 72-hour. Patients receive PCA morphine for moderate to severe pain. Nausea, vomiting and rescue antiemetics are documented.

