***Outcome measures***

Though acute pain is identified as an important predictor for the development of CPSP, advanced pain management strategies have failed to reduce the overall incidence of CPSP, suggesting a complex underlying mechanism. Evidence has demonstrated that pain-related functional interference and patient-reported outcomes, such as quality of recovery, might be associated with the development of CPSP. Thus, the primary outcome of this study is the Quality of Recovery (QoR-15) score at 24 hours after extubation. QoR is recommended for patient's comfort after surgery, and is highly valid and reliable patient-centred outcome measure.

Secondary outcomes include Numerical Rating Scale (NRS) pain scores at 2-hour, 4-hour, 8-hour, 12-hour, 24-hour, 48-hour and 72-hour after extubation, patient satisfaction with pain management and postoperative morphine consumption at the above time points, the time for first morphine rescue (in minutes), intraoperative opioids consumption (converted into morphine equivalence), duration of mechanical ventilation, length of stay in ICU and hospital, side effects associated with opioids such as postoperative nausea and vomiting (PONV), incidence of CPSP at 3-month, 6-month and 12-month, and pain interference measured with Short-Form McGill Pain Questionnaire-2 (SF-MPQ-2) and Brief Pain Inventory (BPI) Interference Scale at 3-month, 6-month and 12-month after surgery.

CPSP is defined as persistent pain after surgery that was not present before surgery or that had different characteristics, and other possible causes of pain are excluded. Participants reported CPSP will further be assessed on the severity and impact of chronic pain based on the recommendations by the Initiative on Methods, Measurement, and Pain Assessment in Clinical Trials (IMMPACT), including the SF-MPQ-2 to assess the sensory pain qualities and affective components, and the BPI to assess the interference of pain with physical functioning.

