### ***Statistics and sample size calculation***

Sample size was calculated using G\*Power software version 3.1.9.3 (Kiel University, Kiel, Germany), based on the QoR-15 score at 24 hours postoperatively — the primary outcome. The minimum clinically important difference (MCID) for the QoR-15 score is eight points, and the typical standard deviation (SD) ranges from 10 to 16. Assuming a two-sided type I error of 0.05, type II error of 0.2, and a population variance of 144 (SD = 12), a sample size of 36 per group is required. Allowing for a 20% dropout rate as a result of loss to follow up after patients discharge, a total of 96 patients (48 patients per group) will provide 80% power to detect a mean difference of  $\geq 8$  points in the QoR-15 score at 24 hours between the two groups.

All outcomes will be analyzed and reported on an intention-to-treat basis, with patients analyzed according to their randomized group regardless of protocol adherence. A secondary per protocol analysis will be conducted for patients who do not adhere fully to the study protocol. Given the repeated measures of pain scores over time, which are correlated,

Generalised Estimating Equation (GEE) models will be used to assess the time effects of postoperative analgesia. Categorical data will be reported as counts and percentages. Continuous variables will be presented as mean (standard deviation) or median (interquartile range), depending on normality assessed using the Shapiro-Wilk's test. Between-group comparison will be conducted using the independent sample *t*-test for parametric data and Mann-Whitney U test for nonparametric data. Categorical variables will be compared using the Chi-square test. Data analyses will be performed using SPSS 27.0 (IBM Corp, Armonk, NY), and GEE modelling will be conducted using Stata V.14 (Statam College Station, Texas, USA), with a Gaussian distribution, identify-link function, exchangeable correlation structure, and robust standard errors. A P-value of  $<0.05$  will be considered statistically significant, without adjusting for multiple comparisons.

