### **Ethics, data management and dissemination**

Patients will be screened for recruitment on the day prior to surgery, and the risks and benefits of the study will be explained. Written informed consent will be obtained from the patient. Patients may withdraw from the project at any time without prejudice. Study participants will be assigned a unique code as identifier throughout the study. All data will be entered into an electronic system by research team members who are trained in data entry. To ensure accurate data entry, a second member of the research team will check data entry. Data collection and study conduct will be monitored with the research team on weekly basis to ensure protocols are implemented consistently. All data will be kept confidential and maintained on a password-protected computer and in locked filing cabinets within the secure offices of the Department of Anesthesia and Intensive Care. Digital files will be securely deleted, and paper documents shredded, after 5 years. Only group data will be published. Access to data will be restricted to study investigators. Approval for the project has been obtained from The Joint Chinese University of Hong Kong-New Territories East Cluster Clinical Research Ethics Committee. The study will adhere to local laws, Declaration of Helsinki, International Council for Harmonization of Technical Requirements for Pharmaceuticals for Human Use Good Clinical Practice and Institutional Policies. All adverse events associated with the study drug will be recorded by the research team and reported to the trial management committee. The trial management committee, comprising external and independent clinicians, will review all events within 48 hours and discuss them at regular trial committee meetings. The results of this study will be disseminated at international conferences and in peer-reviewed journals.

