## Appendix A

The following medical and surgical data during the hospital stays will be extracted from electronic record:

1. Patient demographics (age, gender, EuroScore)
2. Type of surgery
3. Duration of surgery and duration of cardiopulmonary bypass
4. ASV time to spontaneous breathing
5. Episodes of nausea and vomiting, and use of rescue antiemetics
6. Length of ICU and hospital stay

|                     |           | STUDY PERIOD    |             |             |             |              |              |              |              |         |         |
|---------------------|-----------|-----------------|-------------|-------------|-------------|--------------|--------------|--------------|--------------|---------|---------|
|                     | Enrolment | Post-allocation |             |             |             |              |              |              |              |         |         |
| TIMEPOINTS          | Baseline  | 2h extubate     | 4h extubate | 6h extubate | 8h extubate | 12h extubate | 24h extubate | 48h extubate | 72h extubate | 3-month | 6-month |
| ENROLMENT:   |           |                 |             |             |             |              |              |              |              |         |         |
| Eligibility screen  | X         |                 |             |             |             |              |              |              |              |         |         |
| Informed consent    | X         |                 |             |             |             |              |              |              |              |         |         |
| Demographic data    | X         |                 |             |             |             |              |              |              |              |         |         |
| Comorbidity data    | X         |                 |             |             |             |              |              |              |              |         |         |
| EuroScore           | X         |                 |             |             |             |              |              |              |              |         |         |
| Allocation          | X         |                 |             |             |             |              |              |              |              |         |         |

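### Re-operation within 24 hours, and remifentanil use as worded, are exclusion criteria that can only be met after randomisation, in conflict with the intention-to-treat rule

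*Protocol*

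**What the plan says.** The last items of the exclusion list in the protocol's Methods are "re-operation within 24 hours after surgery, intraoperative use of remifentanyl, and inability to provide informed consent".

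The order of events is given in four other places:

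- Ethics, data management and dissemination: "Patients will be screened for recruitment on the day prior to surgery".
- Appendix A marks allocation in the baseline column under enrolment. The extubation time points and later visits come under "Post-allocation".
- Anaesthesia and Interventions: "ITPB is performed after anaesthesia induction with the patient in lateral decubitus positioning".
- The same section, on opioids: "Intraoperative opioids (fentanyl and morphine) will be administered at the discretion of the anaesthesiologist". Intraoperative opioid consumption is a listed secondary outcome.

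The analysis rule, in Statistics and sample size calculation, is: "All outcomes will be analyzed and reported on an intention-to-treat basis, with patients analyzed according to their randomized group regardless of protocol adherence". A secondary per-protocol analysis follows. No section says whether a randomised patient who is re-operated on, or who receives remifentanil, stays in the intention-to-treat set, is replaced, or leaves only the per-protocol set.

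**The concern.** An exclusion criterion should rest on facts known before allocation. A criterion that can be met only afterwards acts as a rule for removing randomised patients. What is left is a subset selected after treatment, and randomisation no longer guarantees that its two arms are comparable.

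The risk is not purely formal. The choice and amount of intraoperative opioid can respond to nociception, which the block is meant to reduce. Re-operation is a complication arising after treatment, and such patients may well recover differently. If either event differs in frequency or in kind between the arms, removing these patients would bias QoR-15 at 24 hours, the primary outcome, as well as opioid use, ventilation time and length of stay.

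**Working it through.** **The plan's own figure.** The inputs are in Statistics and sample size calculation: difference 8, SD 12 (variance 144), and "Assuming a two-sided type I error of 0.05, type II error of 0.2".

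- Normal approximation: n = 2(1.960 + 0.842)² × 144/64 = 2 × 7.85 × 2.25 = 35.3, so 36 per group, as stated.
- Two-sample t-test: 36.3, so 37 per group.
- With 20% dropout: 36/0.8 = 45, or 37/0.8 = 46.25, so 47 per group. The stated 48 per group (96 in total) is slightly conservative.

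The sample size is not in dispute. The allowance is attributed only to loss to follow-up after discharge, so it was not set to cover these removals.

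**When each exclusion can be known.**

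| Criterion | Known at screening, the day before surgery? |
|---|---|
| Emergency or redo surgery | Yes |
| Chronic pain, chronic opioids or sedatives | Yes |
| Renal function below the limit | Yes |
| Unable to consent | Yes |
| Remifentanil during surgery | No as worded; yes if planned use is meant |
| Re-operation within 24 hours | No, on any reading |

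Redo surgery is a separate item, so the re-operation criterion cannot refer to a previous operation. The protocol does not state when the envelope is drawn. Allocation must still come before the study syringes are prepared, and the block comes before the operation. A patient re-operated on within 24 hours has therefore been both randomised and injected.

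**The two rules applied to one patient.** Take a patient returned to theatre 10 hours after surgery. The exclusion list says this patient is not in the trial. The statistics section says the patient is analysed in the randomised group. No text says which rule prevails.

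**Power, under assumed rates.** Let a share e of each arm be excluded on top of 20% dropout. Evaluable n per arm = 48 × 0.8 × (1 − e). Power is for the t-test with difference 8 and SD 12.

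| e (assumed) | n per arm | Power |
|---|---|---|
| 2% | 37.6 | 81% |
| 5% | 36.5 | 80% |
| 10% | 34.6 | 78% |
| 15% | 32.6 | 76% |

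The loss of power is small.

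**Bias, under assumed rates.** If shares e₁ and e₀ of the two arms are removed, and those patients score d points below the patients retained in their arm, the group difference shifts by (e₁ − e₀) × d.

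- Equal shares and equal d: shift 0.
- 2% against 10%, d = 10 to 20: 0.08 × 10 = 0.8, to 0.08 × 20 = 1.6 points.
- 1 of 48 against 4 of 48, d = 20 to 30: 3/48 × 20 = 1.25, to 3/48 × 30 = 1.88 points. This is 1.25/8 = 16% to 1.88/8 = 23% of the 8-point difference.

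The shift favours the block if more low scorers leave the block arm, and goes against it if more leave the control arm.

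**The case against.** The best defence is that the sections can be read together: these events count as departures from protocol, everyone stays in the intention-to-treat analysis, and only the per-protocol set shrinks. Nothing in Methods says that randomised patients are withdrawn or replaced. That would be a sound plan, but it is not what is written. The two items stand among the eligibility criteria, and a team following that list would remove the patients. A statistical analysis plan, which is not available here, could define the analysis sets, but it would not mend the eligibility wording.

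Other objections stand and limit the point:

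- **Remifentanil.** The interventions section names fentanyl and morphine as the intraoperative opioids, so the item may mean patients whose anaesthetic plan includes remifentanil. That could be known before allocation. The text says use, not planned use, so the item is ambiguous rather than plainly wrong.
- **Selection on outcome.** A reader might infer that patients are removed by outcome. Neither event is itself a listed outcome. Remifentanil use comes close, since intraoperative opioid consumption is one. The accurate term is post-randomisation event.
- **Unequal removal.** A reader might infer that the arms would lose patients unequally. The documents give no rates and no mechanism by which the block would change re-operation. The block operator, care team and data recorders are blinded, which limits deliberate selection. Blinding does not stop the block itself from affecting opioid need.
- **Concealed complications.** A reader might infer that early complications would go unreported. Adverse events associated with the study drug are to be recorded and reviewed within 48 hours by an independent committee, and nothing says that excluded patients are left out.

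**Conclusion.** The point holds for re-operation within 24 hours on any reading, and for remifentanil as worded. Followed literally, the exclusion list would remove patients already randomised and treated, against the protocol's own intention-to-treat rule. This is a conflict in stated text about who enters the primary analysis, and so more than a missing detail.

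The size of any bias is unknown and could be nil. The shifts of 0.8 to 1.6 and 1.3 to 1.9 points rest wholly on assumed, unequal removal and assumed score deficits. They show that a shift that matters beside 8 points is possible, not that it is expected. Power is a minor matter: about 81% to 76% for an assumed 2% to 15% removal on top of dropout. What is at stake is the randomised comparison.

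**What to change.** Reconcile the exclusion list with the statistics section:

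- Remove re-operation within 24 hours from the eligibility criteria.
- Either remove the remifentanil item or reword it as a fact known before allocation, namely planned use.
- State that every randomised patient stays in the intention-to-treat set, with QoR-15 and follow-up still collected. If a re-operated patient is ventilated again, state which extubation starts the 24-hour clock.
- Report both events by arm as post-randomisation events, and use them only to define the secondary per-protocol set.

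None of this bears on which opioid to give or when to re-operate. The cost is a short amendment and possibly slightly higher variance from the patients retained. The planned 96 need no change. The amendment should be made before any patient is removed under the present wording and before any unblinding.
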